### Clinical eye examination

The CarMeR study will include a clinical eye examination. The clinical eye examination will be done to assess the status of some selected visual functions and then to screen for visual outcomes that may have been affected by impaired glucose tolerance (IGT). The examination protocol comprises of habitual distant visual acuity measurements, habitual near visual acuity measurements, contrast sensitivity measurement, central visual field measurements, an internal and external eye examination, and assessment of the visual disability index of participants. A qualified optometrist will determine the visual acuity of participants using a Bailey-Lovie or Early Treatment Diabetic Retinopathy Study (ETDRS) visual acuity chart. This is done monocularly at a testing distance of 4 meters with the participants’ usual distance correction. Habitual near visual acuity will also be assessed at 40 cm and recorded in log MAR.

Internal and external eye examination procedures are performed by a qualified optometrist based on the rapid assessment of avoidable blindness (RAAB) methods (54, 55). During this external examination, the eyelids, eyelashes, the eye globe, and anterior segment of the eye are examined. For the internal examination, the main structures to be examined are the lens and the retina. The general retinal area is observed, and the presence or absence of signs of diabetic retinopathy is noted and graded using the International Clinical Diabetic Retinopathy Disease Severity Scale (56). The same is done for the macula and the presence or absence of signs of diabetic macular edema is noted and graded based on the International Clinical Diabetic Macular Edema Disease Severity Scale (56). This is done using the Welch Allyn ophthalmoscope (Welch Allyn, US).

Central Visual Field (CVF) testing is done using the black on white (BOW) Amsler Chart at a distance of 33cm. This is done with the participant’s habitual visual acuity and with near correction, if needed. If any abnormalities such as scotoma, blurry lines, irregular patches, or metamorphopsia are identified, it is categorized as a positive result and the area of visual field is computed. Contrast sensitivity (CS) testing is performed using the Pelli-Robson chart (57). Testing for CS is done at 1 meter where each correctly identified letter receives a score of 0.05 log units, except for the initial triplet. Participants who are deemed to be visually impaired are then administered the visual disability questionnaire (VDQ) adapted from a study on diabetic retinopathy (51). The visual disability score or index is calculated as the mean score within each category, and the sum is calculated for each participant.

Visual impairment classification is determined by visual acuity and visual field, based on the 11th revision of the International Statistical Classification of Diseases, Injuries, and Causes of Death (ICD11) by the World Health Organization (WHO). Mild visual impairment comprises of visual acuity worse than 0.3 log MAR to 0.5 log MAR in the better seeing eye, moderate to severe visual impairment (MSVI) comprises visual acuity worse than 0.5 log MAR to 1.30 log MAR in the better seeing eye, and blindness comprises of visual acuity worse than 1.30 log MAR in the better seeing eye (58).

### Biochemical measurements

#### Fasting blood collection and processing

Eligibility for participating in the OGTT requires participants to fast for at least eight hours, with permission to drink plenty of water from 8pm the night before sample collection. Medical Laboratory Scientists licensed by the Allied Health Profession Council of Ghana will collect the blood specimen using standard venipuncture techniques, with a vacuum blood collection system. Fasting blood specimen of 3ml is collected into one gel separator tube and 2ml each of fasting blood is collected into separate fluoride oxalate tubes for HbA1C and FPG analysis. The blood specimens are kept on ice and transported to the lab for processing and storage. An initial fasting blood glucose test is performed using an Accu-Chek Instant meter and Accu-Chek Instant test strip (Roche, Germany, 2019) to determine glucose tolerance levels and the safety of the participants before subsequent glucose administration for the OGTT procedure. Blood specimen for the other biochemical measurements in this study are also collected in the gel separator tube. These specimens are separated at 3000rpm for 3 minutes and the serum aliquoted into Eppendorf tubes for blood chemistry analysis, immunoassay analysis and storage for reference. For the specimen in the two fluoride oxalate tubes, one is separated and the plasma is aliquoted into Eppendorf tubes and used for fasting blood glucose analysis, whereas the other fluoride oxalate tube sample is used for HbA1c analysis.

To assess the glucose metabolism of participants, an Oral Glucose Tolerance Test (OGTT) is performed as a gold standard diagnostic test. The OGTT assessment uses three time points where blood samples are collected at glucose time of 0, 60 and 120 minutes. The glucose 0’ blood specimen is taken and 82.5g of dextrose monohydrate (equivalent to 75g of anhydrous glucose) is dissolved in 250 ml of drinking water for the participants to drink within 3 minutes. While waiting for their blood to be collected, participants were monitored for any adverse reactions by a trained medical officer. After which blood specimens are taken twice more to assess OGTT glucose level values at 60 minutes and 120 minutes. Each of the time points will be used to diagnose glucose tolerance levels. Prior to the OGTT procedure, spot whole blood glucose analysis is performed to assess Fasting Blood Glucose (FBG). At baseline, blood specimen is also drawn to measure glycated hemoglobin (HbA1C) levels, inflammations (high-sensitivity C-reactive protein [hsCRP], interleukin 6 [IL6]), lipid panels (serum cholesterol, plasma HDL, LDL, TG) and cortisol (a measure of physiologic stress). Specimens for creatinine, liver function tests (AST and ALT), and total protein levels are also taken to measure kidney and renal function. For the OGTT procedure, 10ml of blood is sampled at each time point from each participant, totaling 30ml per participant.

#### Specimen analyses

Spot whole blood glucose analysis is performed using an Accu-Chek Instant meter and Accu-Chek Instant test strip (Roche, Germany, 2019) to determine fasting blood glucose levels. Blood chemistry and Plasma Glucose analysis are conducted using the Mindray BS-240 Blood chemistry analyzer (Mindray, China, August 2022). Glycated hemoglobin (HbA1c), high-sensitivity C-Reactive Protein (hsCRP/CRP), IL6 and Cortisol levels are analyzed using the Wondfo Finecare III Plus Fluorescent Immunoassay analyzer (Wondfo, China, June 2022).

#### Diagnoses

Diagnosis of abnormal glucose tolerance in the CarMeR study will be done using fasting plasma glucose (FPG), HbA1c and OGTT diagnostic tests based on the criteria suggested by the International Experts Committee Report on Diabetes and American Diabetes Association (59, 60). Participants are classified as having prediabetes if they have an FPG level between 5.6mmol/L and 6.9 mmol/L (100mg/dl and 125mg/dl), or an HbA1c level between 5.7% and 6.4% or a 2-hour OGTT result between 140mg/dl and 199mg/dl. Participants are classified as having diabetes if they have an FPG level of 7.0 mmol/L or higher (126mg/dl or higher), or HbA1c level of 6.5% or higher, or a 2-hour OGTT result of 200mg/dl or higher. Additionally, 1-hour post load plasma glucose (PG) will be used to diagnosed hyperglycemia (IH) and diabetes. Participant with a 1-h PG ≥ 155 mg/dL (8.6 mmol/L) are considered to have IH and should be prescribed lifestyle interventions and referred to a diabetes prevention program. Participants with a 1-h PG ≥ 209 mg/dL (11.6 mmol/L) will be considered to have diabetes. Generalized obesity is defined as body mass index (BMI) ≥30 kg/m^2^, and central obesity as a waist circumstance >102 cm in men or >88 cm in women, and a waist-to-hip (WHR of 0.88-0.89 (61, 62). Certified medical laboratory diagnostic scientists will perform all blood sample analysis at the Cardiometabolic Epidemiology Research Laboratory (CERL).

### Recruitment and training of research assistants

The CarMeR study uses two PhD and two MPhil students as research assistants, along with four Laboratory Diagnostic scientists in the study. The four students will be trained on how to establish rapport with the participants, describe the study, collect informed consents with the help of the PI and Co-PI, conduct anthropometric measurements according to the protocol, and administer the survey questionnaire. Laboratory Diagnostic Scientists will be oriented on the specific blood specimen to draw and the corresponding analyses to be performed.

### Enrollment visit

Prior to data collection, recruitment of participants is done by the research assistants (RAs). This is achieved through community engagement via the identified gatekeepers of the specific community. The gatekeepers subsequently organize their community members to engage with the research team. The RAs recruit eligible participants based on the inclusion criteria. The selected participants are assigned codes to anonymize them, and their contacts are collected. Participants who meet the inclusion criteria and agree to participate in the study are asked to sign an informed consent form. Prior to the day of the data collection, participants are called on phone and are reminded of the requirement to fast (8-12 hours), and not ingest any other fluid apart from water. Participants arrive at the study site at 6:30am as communicated to them, and they are asked to rest for a while before their vital signs were measured. Anthropometric measurements are taken, followed by baseline blood samples for FBG, creatinine, liver function tests (AST and ALT), and lipid profiles. After which, a three-point OGTT is performed to assess glucose tolerance. The whole and plasma blood samples are then sent to the CERL at University of Cape Coast, Ghana for analysis and preservation in a cryogenic freezer -40°C. The entire duration of the process is expected to last four hours. Subsequently, participants newly diagnosed with diabetes using a 2-hour glucose level between 11.1-17.0mmol/L (200-299mg/dL) are put into one cohort to complete 12 months lifestyle intervention program and monthly follow-ups. While participants identified with 2-hour glucose ≥ 17.0mmol/L (≥300mg/dL) are referred for medical treatment.

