## Methods

The CarMeR Study will be executed by a multidisciplinary team of researchers from the University of Cape Coast, its Directorate of Health Services, the Rwanda National Hospital, and the University of Global Health Equity, Rwanda. To obtain reliable and valid results, the CarMeR Study will adhere to gold standards in all aspects of the project, including but not limited to the selection of communities, standardization of study protocols, adherence to ethical principles in the sampling procedures, anthropometric measurements, blood glucose testing, chemistry measurements, eye examination, blood pressure measurements, and surveys. The CarMeR Study will adopt the WHO-STEPwise approach for assessing cardiometabolic risk factors The STEPwise approach to surveillance (STEPS) is an NCD surveillance tool recommended by the WHO since 2005 for monitoring trends across countries (38, 39). The WHO-STEPwise instrument comprises three distinct phases or “steps” for evaluating risk factors. The first step is a questionnaire-based assessment, the second step comprises of physical measures and the third step comprises of biochemical measures (40). This instrument is a simplified and standardized approach to surveillance for collecting, analyzing and disseminating data on key risk factors especially for NCDs (38). In addition to a questionnaire survey, a community-based quasi-experimental design will be utilized to assess the glucose tolerance of all participants after administration of 82.5g monohydrate dextrose, in order to ascertain the prevalence and risk factors for undiagnosed diabetes and prediabetes. Subsequently, all consenting participants diagnosed with abnormal glucose tolerance will be enrolled into a community-based randomized controlled trial (RCT) to measure the effectiveness of lifestyle interventions on diabetes remission.

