#### Inclusion criteria

Participants would be included in the study if they aged 25 to 70 years, and have not been diagnosed with prediabetes or diabetes. Additionally, participants should be willing to undergo the screening procedure (glucose testing, eye examination, BMI assessment, lipid level measurement, and body composition analysis). Participants diagnosed of diabetes based on a 2-hour OGTT glucose level between 11.1-17.0mml/L (200-300mg/dL) or prediabetes with 2-hour OGTT glucose level between 7.8-11.0 mmol/L (140-199mg/dL), would be followed up with a non-pharmacological lifestyle intervention for one year to assess the effect on their glucose tolerance.

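### The lifestyle phase has two entry rules that cannot both be followed, and its referral limit of 17.0 mmol/L is printed as 300 mg/dL when it is 306 mg/dL

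*Protocol article*

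**What the plan says.** Four parts of the Protocol article bear on who enters the one-year lifestyle phase.

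- **Methods, opening text:** "all consenting participants diagnosed with abnormal glucose tolerance will be enrolled into a community-based randomized controlled trial (RCT". No 2-hour range and no upper limit is attached.
- **Diagnoses:** "Diagnosis of abnormal glucose tolerance in the CarMeR study will be done using fasting plasma glucose (FPG), HbA1c and OGTT diagnostic tests". The criteria are alternatives, so any one is enough: "Participants are classified as having diabetes if they have an FPG level of 7.0 mmol/L or higher", "or HbA1c level of 6.5% or higher, or a 2-hour OGTT result of 200mg/dl or higher". A 1-hour value of 209 mg/dL (11.6 mmol/L) or more also counts as diabetes. A 1-hour value of 155 mg/dL (8.6 mmol/L) or more leads to lifestyle intervention and referral to a diabetes prevention programme.
- **Inclusion criteria:** follow-up with the intervention is given by 2-hour band: "Participants diagnosed of diabetes based on a 2-hour OGTT glucose level between 11.1-17.0mml/L (200-300mg/dL"), "or prediabetes with 2-hour OGTT glucose level between 7.8-11.0 mmol/L (140-199mg/dL").
- **Enrollment visit:** participants "newly diagnosed with diabetes using a 2-hour glucose level between 11.1-17.0mmol/L (200-299mg/dL) are put into one cohort" for the 12-month programme. The upper limit follows: "While participants identified with 2-hour glucose ≥ 17.0mmol/L (≥300mg/dL) are referred for medical treatment". This section names no route for prediabetes.

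**The concern.** The broad rule and the 2-hour rule describe different sets of people, and nothing in the article says which one prevails. The entry rule fixes the population of objective 6, which asks whether lifestyle change leads to reversal or prevention. For some participants it also leaves open whether they start as diabetes or prediabetes. The practitioner on site can settle a single case, but not which set of people makes up the trial.

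The referral limit separates a year of lifestyle intervention from medical treatment in someone newly diagnosed. Such a limit needs one meaning, whichever unit the laboratory reports.

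**Working it through.** **1. Entry rule: the sections side by side.** Take consenting participants who complete the OGTT as planned (values in mmol/L).

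| Participant | Diagnoses | Methods | Inclusion criteria | Enrollment visit |
|---|---|---|---|---|
| FPG 7.4, 2-hour 7.2 | diabetes | enrolled | no band | no band |
| FPG 7.4, 2-hour 9.0 | diabetes | enrolled | followed up as prediabetes | no route named |
| 2-hour 18.0 | diabetes | enrolled (no upper limit) | above the band | referred |

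The first person may also be sent to lifestyle intervention by the 1-hour sentence in Diagnoses, depending on a third value. That section does not say whether this means the trial or something outside it.

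**2. Referral limit: the unit check.** The conversion factor is not printed, but the article's other glucose pairs imply it:

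- Diagnoses: 100/5.6 = 17.86; 125/6.9 = 18.12; 126/7.0 = 18.00; 155/8.6 = 18.02; 209/11.6 = 18.02.
- Inclusion criteria: 140/7.8 = 17.95; 199/11.0 = 18.09; 200/11.1 = 18.02.

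All eight agree with a factor of 18.016 to the printed decimal. The referral pair does not: 300/17.0 = 17.65. Converting each way:

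- 17.0 × 18.0 = 306.0 mg/dL; 17.0 × 18.016 = 306.3 mg/dL.
- 300/18.0 = 16.67 mmol/L; 300/18.016 = 16.65 mmol/L.
- A 2-hour value of 16.8 mmol/L is 16.8 × 18.0 = 302.4 mg/dL. It is below 17.0 mmol/L (lifestyle) and above 300 mg/dL (treatment).

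The edges also clash. Exactly 17.0 mmol/L lies in both bands of Enrollment visit. Exactly 300 mg/dL is lifestyle in Inclusion criteria (200-300) and referral in Enrollment visit (200-299).

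**3. How many people the unit error touches.** The article gives no distribution of 2-hour values, so this is a range built on assumptions.

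- Diabetic by any criterion: 78 (6.5% of 1200, inside the 6-7% in the Participants section) or 120 (10% of 1200, the proportion in the sample-size statement).
- Share of these at or above 11.1 mmol/L at 2 hours: assumed 50% to 80%. This gives 78 × 0.5 = 39 up to 120 × 0.8 = 96 people.
- Disputed zone: 16.65 to 17.0 mmol/L, width 0.35.
- Values spread evenly over 11.1 to 22 mmol/L: 0.35/10.9 = 3.2%, so 39 × 0.032 = 1.3 up to 96 × 0.032 = 3.1 people.
- Values falling off exponentially above 11.1 with mean excess m: exp(−5.55/m) − exp(−5.90/m) = 1.0% (m = 2), 1.7% (m = 3), 2.2% (m = 5). This gives 39 × 0.010 = 0.4 up to 96 × 0.022 = 2.1 people.

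Taken together, the range is about 0.4 to 3.1 people.

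**The case against.** The best defence is that the Methods sentence is an overview, while Inclusion criteria is the specific rule. Enrollment visit agrees with it that the 2-hour value selects the diabetes group, so a reader would let the specific rule govern. This has force, and it points to a light repair. It does not remove the conflict, because Diagnoses ties abnormal glucose tolerance expressly to all three tests, Methods then enrols on that term, and the two specific sections themselves differ on prediabetes.

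It can also be said that people positive on one test and negative at 2 hours may be rare. That cannot be ruled out: if every case were positive at 2 hours, no diabetes case would turn on fasting glucose or HbA1c. Yet objective 5 exists because the tests are expected to disagree.

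A reader might infer that a sizeable, known share of the trial is at stake. The documents do not support that. They give no overlap between tests, and someone with a 2-hour value of 7.8 to 11.0 mmol/L is followed up under Inclusion criteria anyway, so only the label is disputed.

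A reader might also infer that the main analysis of objective 6 depends on the starting label. The Data analysis section plans a linear mixed model on glucose biomarkers, adjusted for baseline characteristics, and t-tests. It does not name the diabetes or prediabetes label as a term. The label matters for describing reversal, not evidently for that model.

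On the referral limit, the fair reply is that it is an editorial slip affecting very few people. That stands as to size.

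**Conclusion.** Both parts hold on the text. The article states an entry rule based on any diagnostic test and another based on the 2-hour value, and they cannot all be followed. The number whose entry differs cannot be derived from the documents, so none is claimed. The referral limit is wrong in one of its two units, and the bands overlap at exactly 17.0 mmol/L and at exactly 300 mg/dL. The disputed zone holds about 0.4 to 3.1 people, assuming 39 to 96 participants are diabetic on the 2-hour value and the distributions tried above.

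Of the two, the entry rule matters more. No bias in the comparison of FPG and HbA1c with the OGTT (objective 5) follows from either part, since every participant is planned to have all the tests whatever the later routing. The wording should be corrected, because the change costs little and the limit decides about treatment.

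**What to change.** (a) State one entry rule in Methods, Inclusion criteria and Enrollment visit. The smallest change keeps the 2-hour rule: consenting participants with 2-hour glucose from 7.8 mmol/L up to the referral limit are enrolled, covering both prediabetes and diabetes. Add to Diagnoses that people diagnosed only on FPG, HbA1c or 1-hour glucose count towards prevalence and are advised or referred outside the trial. This also settles where the 1-hour sentence leads.

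(b) Print one referral limit, identically in Inclusion criteria and Enrollment visit, with lifestyle strictly below it. It can be 300 mg/dL (16.7 mmol/L), the more cautious choice, or 306 mg/dL (17.0 mmol/L). The text does not show which was intended, so the investigators must choose.

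The cost is a few sentences in four sections, with no new sample or visit. The trial becomes somewhat smaller than the Methods sentence implies. With 16.7 mmol/L, up to about three people move from lifestyle to treatment under the assumptions above.

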### Data analysis

For the accuracy of data and information, data collected through the Kobo Collect toolbox application will be downloaded into an Excel spreadsheet and screened visually and statistically. Data will be analyzed and interpreted by the principal investigator and his local collaborators and shared back with foreign collaborators. In the attempt to make the findings of the study public, data analysis will be conducted using STATA 16 and SPSS 23. Statistical tools specific and relevant to the research questions and hypotheses of the CarMeR study would be used. To determine the prevalence of undiagnosed diabetes, prediabetes and other associated cardiovascular risks, data on OGTT, FPG and HbA1c will be analyzed using descriptive statistics (percentages and confidence intervals). In order to investigate the differences in phenotype, diabetes, prediabetes, and normoglycemic groups will be compared based on BMI and body composition (waist hip ratio, body fat percentage, skeletal muscle, total body water) using analysis of variance (ANOVA) and t-test. To profile the ocular characteristics and complications of the diabetes and prediabetes groups, a cross-tabulation and a subsequent chi-square test will be done to assess the association between glycemic dysregulation and the presence of ocular complications (diabetic retinopathy, cataract, macular edema). For the purpose of ascertaining whether the predominant etiological factor of undiagnosed diabetes in this populations is insulin resistance or beta-cell failure, a homeostasis model analysis of beta [HOMA-β and HOMA-IR] will be computed and logistic regression will be used to determine the dominant factor. As a way of determining the sensitivity of other diagnostic alternatives (FPG and HbA1c) in comparison to the multi-sampled OGTT, receiver-operated characteristics (ROC curves), including sensitivity and specificity curves, will be used. Finally, to ascertain whether lifestyle changes (food choice, physical activity, weight loss, psychosocial counseling) over a one-year period impacts biomarkers of glucose regulation, a linear mixed model regression analysis, controlled for baseline characteristics will be used. T-tests will be conducted to observe changes in glucose regulation biomarkers.

To manage missing data, imputation and deletion methods would be employed. When the percentage of the missing data is low and not across all observations, the imputation method would be used to estimate the missing data. However, where the number of missing data points is high or the entire data point is missing information, the data point would be deleted during analysis to reduce bias.

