**Figure 1 f1:**
[figure not shown]
A conceptual framework for the CarMeR Study.

This project, dubbed the Cardiometabolic Risks (CarMeR) Study, is by the Bill and Melinda Gates Foundation through the African Postdoctoral Initiative, managed by the African Academy of Sciences. The objectives are: 1. determine the prevalence of undiagnosed diabetes, prediabetes and other associated cardiovascular disease risks using the multi-sampled oral glucose tolerance test [OGTT] with 82.5g monohydrate dextrose, 2. characterize the phenotype of diabetes and prediabetes relative to body composition, body mass index (BMI), and other anthropometric measures, 3. establish the ocular characteristics and complications in people with diabetes and prediabetes, 4. ascertain whether the etiology of undiagnosed diabetes is predominantly insulin resistance or beta-cell insufficiency using homeostasis model analysis of beta [HOMA-β and HOMA-IR], 5. determine the sensitivity of diagnostic alternatives to the multi-sampled OGTT, specifically the fasting plasma glucose (FPG) test and the glycated hemoglobin (HbA1c) test, and 6. determine, over a 1-year period, if changes in food choices, physical activity, weight loss and psychosocial counseling influence reversal or prevention among people newly diagnosed with diabetes and prediabetes.

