### Population

The population comprises adults aged between 25 and 70 years living in households within the Cape Coast metropolis. The choice of this age range was influenced by the fact that they are at a higher risk of developing diabetes in the metropolis (41, 42). It is estimated that the number of people between the ages of 25 and 70 living in the Cape Coast Metropolis is 102,533 (43), spread across several households and communities in the metropolis. The sample for the study is being drawn from rural, peri-urban, and urban communities in the Cape Coast Metropolis. Owing to the heterogeneous nature of the Cape Coast population, the selection of participants for this study is based on different characteristics. These characteristics includes the type of community (rural, peri-urban, urban), main economic activity (farming, fishing, trading, formal work), dominant religion (Christianity, Islam, African traditional religion), and ethnicity (Fante, Ewe, Asante, northern tribes).

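### Body composition and ocular complications are compared across glycaemic groups with crude tests only, so age and sex could produce differences that are then attributed to dysglycaemia

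*Protocol article*

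**What the plan says.** All references are to the protocol article.

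- **Phenotype objective (objective 2), Data analysis.** The "diabetes, prediabetes, and normoglycemic groups will be compared based on BMI and body composition", with waist-hip ratio, body fat percentage, skeletal muscle and body water as the body-composition measures, "using analysis of variance (ANOVA) and t-test".
- **Ocular objective (objective 3).** The aim, given at the end of the Introduction, is to "establish the ocular characteristics and complications in people with diabetes and prediabetes". Data analysis says that "a cross-tabulation and a subsequent chi-square test will be done to assess the association between glycemic dysregulation and the presence of ocular complications". The complications it names are "diabetic retinopathy, cataract, macular edema".
- **Lifestyle objective (objective 6), Data analysis.** Here "a linear mixed model regression analysis, controlled for baseline characteristics will be used". No other analysis in the section has stated adjustment.
- **Population.** "The population comprises adults aged between 25 and 70 years living in households", and "The choice of this age range was influenced by the fact that they are at a higher risk of developing diabetes".

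The Abstract lists the same tests. Neither place mentions covariates, stratification or matching by age or sex for objectives 2 and 3.

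**The concern.** A chi-square test on a cross-tabulation and a one-way ANOVA have no place for a covariate. If people with dysglycaemia are older on average, they will have more cataract for that reason alone. If the groups differ in their share of women, their mean body fat, muscle mass and body water will differ for that reason alone. The planned tests cannot tell either situation from a link with glycaemia.

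The article gives partial support for the premises. It ties the chosen age range to diabetes risk (Population), lists sex among the biological determinants of disease (Introduction, biopsychosocial model) and uses different waist cut-offs for men and women (Diagnoses). The link between age and cataract is general knowledge and is not stated in the article.

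At stake is the reading of two of the six objectives. The section on the eye examination speaks of visual outcomes that glucose intolerance may have affected, and Expected outcomes plans to identify the ocular complications that go with abnormal glucose tolerance. The Discussion also faults earlier Ghanaian studies for leaving other influential factors out of account, and the crude tests would share that weakness.

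**Working it through.** **No planned figure to reproduce.** The article gives no sample size, effect size or power for the ocular or body-composition comparisons. The check therefore asks how often the planned tests reject when dysglycaemia has no effect on the outcome given age and sex.

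**Inputs from the article.** Age 25-70; three glycaemic groups; about 1000 participants after attrition, 1200 recruited; expected prevalence of undiagnosed diabetes 6-7%.

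**Assumed inputs.** Age uniform over 25-70, equal numbers of men and women, and every strength of association. Ranges are shown because the article gives none.

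**Step 1. Cataract-like outcome, three groups, N = 1000.** The outcome has about 6% prevalence at mid-age. Age drives dysglycaemia and the outcome separately.

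| Odds ratio per 10 years: dysglycaemia | Odds ratio per 10 years: outcome | Crude chi-square rejects at 5% | Median spurious odds ratio, diabetes vs normal | Age-adjusted logistic test rejects |
|---|---|---|---|---|
| 1.0 | 2.5 | 5.6% | 1.03 | 5.8% |
| 1.6 | 1.0 | 4.3% | 1.05 | 4.0% |
| 1.2 | 1.5 | 8.9% | 1.22 | 4.8% |
| 1.4 | 2.0 | 24.0% | 1.57 | 4.8% |
| 1.6 | 2.5 | 64.4% | 2.03 | 5.8% |

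The crude rates come from 800 samples each and the adjusted rates from 400. The Monte Carlo standard error of a 5% rate at 400 samples is √(0.05 × 0.95/400) = 1.1 points, so the adjusted rates agree with the nominal 5%. A repeat of three of these settings with 3000 samples gave 6.4% (1.2 and 1.5), 25.2% (1.4 and 2.0) and 64.2% (1.6 and 2.5). The weakest setting is thus only slightly above nominal.

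**Step 2. Diabetes against the rest, N = 1200** (diabetes 6.5%, cataract 10%). Odds ratios per decade of 1.4 and 2.5 give a crude odds ratio of 1.47 and 22% rejection; 1.8 and 3.5 give 2.06 and 61%; 1.2 and 1.5 give 1.12 and about 7%.

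**Step 3. Body fat percentage, three groups, N = 1000.** Standard deviation 7 within sex; group cut-offs on a logistic scale at 0.75 and 2.45. With no sex effect these put 1/(1+e^2.45) = 7.9% in the diabetes group and 1/(1+e^0.75) − 7.9% = 24.1% in the prediabetes group.

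Spurious difference = sex gap × (share of women in diabetes group − share of women in normal group).

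For a sex odds ratio of 2, the shares are 65.4% and 44.4%, a difference of 0.210 before rounding. A 12-point sex gap gives 12 × 0.210 = 2.5 points, and an 8-point gap gives 8 × 0.210 = 1.7 points. For a sex odds ratio of 1.25 the shares are 55.1% and 48.2%, giving 0.069 × 8 = 0.6 and 0.069 × 12 = 0.8 points. The simulation agrees:

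| Sex odds ratio for dysglycaemia | Sex gap (points) | Crude ANOVA rejects at 5% | Spurious difference (points) | Sex-adjusted F test rejects |
|---|---|---|---|---|
| 1.0 | 8 | 5.9% | 0.1 | 6.0% |
| 1.25 | 8 | 9.8% | 0.6 | 5.7% |
| 1.5 | 12 | 39.2% | 1.4 | 4.4% |
| 2.0 | 8 | 63.1% | 1.7 | 4.6% |
| 2.0 | 12 | 86.0% | 2.5 | 5.0% |

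**Step 4. Cell counts.** At 6.5% of 1200 there would be 78 people with diabetes. An expected count of 5 in the cell for diabetes with a complication needs an overall complication prevalence of 5/78 = 6.4%. The article gives no prevalence for retinopathy or macular edema, so this step cannot say on which side of that line the data will fall.

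**The case against.** The best defence is that these objectives are largely descriptive. The article uses the language of profiling, differences and association, and a crude comparison is a legitimate description of who has dysglycaemia; adjustment answers a different question. That stands for the tables and group means. It does not stand for the significance tests, whose results the article means to use to identify complications that go with abnormal glucose tolerance.

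A second defence is that adjusted models may sit in a fuller protocol or analysis plan. That is possible. But the article fixes a named crude test for each objective and states adjustment, in the same paragraph, where it wants it. The point concerns that stated choice and not an omitted detail.

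Third, the magnitudes are assumed throughout. This is correct: if age or sex is unrelated to either side, the crude tests hold their level.

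A reader might go further in three ways that the article does not support:

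- **That age and sex differences will be reported as effects of dysglycaemia.** The article does not call these comparisons effects. What it supports is that differences could be attributed to dysglycaemia.
- **That all three eye complications are equally exposed.** Diabetic retinopathy and diabetic macular edema are graded on diabetes-specific scales, so age alone is a weaker mechanism there. Cataract carries the ocular argument.
- **That the chi-square cells will often be too small.** The figure of 78 counts diabetes only, while the planned test concerns dysglycaemia, which includes prediabetes, and no complication prevalence is given. Sparse cells are a matter for the observed counts.

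**Conclusion.** The concern holds in a limited form. As written, the tests for objectives 2 and 3 are crude and can yield confounded associations, chiefly for cataract (through age) and for the sex-dependent body-composition measures. The direction is clear provided that age or sex is related to both glycaemic group and outcome.

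The size is not known. Over the assumed ranges, false-positive rates run from about 6-9% to 64% for the cataract-like outcome and from about 10% to 86% for body fat, with spurious odds ratios of about 1.2 to 2.0 and spurious differences of about 0.6 to 2.5 points. After adjustment the rates are about 4-7%. These ranges show what could happen and are not a forecast for this sample. The change should be made, because it costs little and removes an avoidable ambiguity.

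**What to change.** Amend the Data analysis section as follows.

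- **Objective 3:** keep the cross-tabulations as description. Base inference on logistic regression of each ocular complication on glycaemic group, with age (continuous) and sex as covariates. If the observed events prove few, use a penalised (Firth) or exact method.
- **Objective 2:** keep the group means as description. Base inference on linear regression or ANCOVA of each body-composition measure on glycaemic group, with age and sex as covariates.
- **Reporting:** show crude and adjusted estimates side by side, so that the descriptive and adjusted questions stay separate.

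The cost is a change of wording and a modest amount of programming. Age is an eligibility criterion, demographic data are already collected by questionnaire, and the statistical packages named in the article fit these models. No additional participants or measurements are needed.
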